## Abstract

**Background:**

International disease management guidelines recommend the regular assessment of depression and anxiety in heart failure patients. Currently there is little data on the effect of screening for depression and anxiety on the quality of life and the prognosis of heart failure (HF). We will investigate the association between the recognition of current depression/anxiety by the general practitioner (GP) and the quality of life and the patients’ prognosis.

**Methods/Design:**

In this multicenter, prospective, observational study 3,950 patients with HF are recruited by general practices in Germany. The patients fill out questionnaires at baseline and 12-month follow-up. At baseline the GPs are interviewed regarding the somatic and psychological comorbidities of their patients. During the follow-up assessment, data on hospitalization and mortality are provided by the general practice. Based on baseline data, the patients are allocated into three observation groups: HF patients with depression and/or anxiety recognized by their GP (P+/+), those with depression and/or anxiety not recognized (P+/−) and patients without depression and/or anxiety (P−/−). We will perform multivariate regression models to investigate the influence of the recognition of depression and/or anxiety on quality of life at 12 month follow-up, as well as its influences on the prognosis (hospital admission, mortality).

**Discussion:**

We will display the frequency of GP-acknowledged depression and anxiety and the frequency of installed therapeutic strategies. We will also describe the frequency of depression and anxiety missed by the GP and the resulting treatment gap. Effects of correctly acknowledged and missed depression/anxiety on outcome, also in comparison to the outcome of subjects without depression/anxiety will be addressed. In case results suggest a treatment gap of depression/anxiety in patients with HF, the results of this study will provide methodological advice for the efficient planning of further interventional research.

## Background

Heart failure (HF) is an increasingly prevalent condition with high mortality and morbidity rates [1]. Dyspnoea, oedema, fluid retention, pulmonary congestion and fatigue comprise common symptoms of HF. Although not necessarily jointly present within each individual patient, these symptoms exert substantial detrimental influences on functional status and quality of life [1-3].

### Psychosocial risk factors

Various studies established the important influence of psychosocial factors on the course and prognosis of HF patients [4,5]. Depression affects 20–40% of patients with HF [6] and is 4–5 times more common in HF than in the general population [7]. Depressive symptoms are associated with a 2–3 fold increased mortality risk and were shown to act independently of biological (classical) risk factors [8,9]. Symptoms of anxiety are reported for 38-70% of patients with congestive heart failure [10].

For this reason national and international HF guidelines recommend the regular assessment of depression [11-15] and anxiety [11,12,15] in heart failure patients. However, even though recent evidence suggests that patients screened positive for depression have an increased risk for hospitalization, emergency department visits and mortality [16,17], there is no data available on the transformation of these recommendations into routine care of HF patients.

Different aspects of psychosocial health (e.g. depression, anxiety, social support) are highly interrelated. It is still unclear which factor or component may independently affect the prognosis of HF patients [5]. We are aware of two randomised controlled trials investigating the effects of selective serotonin re-uptake inhibition on morbidity, mortality and mood in depressed patients with HF [18,19]. While the MOOD-HF study is still on-going [18], the SADHART-CHF trial concluded that the lack of effects of sertraline, compared to placebo treatment, may be due to the effect of nurse support within the placebo group, where depression scores improved significantly [19]. However, these trials focus on pharmacological interventions in a tertiary care setting. There are no interventional studies in primary care examining complex interventions such as screening for depression/anxiety (and subsequent treatment initiated by the general practitioner) in HF patients. There are also no studies that examined the effect of recognition and subsequent treatment of depression/anxiety initiated by the general practitioner (GP) once depression and or anxiety have been recognized. Therefore, it will be important to determine whether there is a need for interventional research targeting the effect of treating depression and anxiety on the prognosis of HF in patients with HF in primary care.

### Recognition of depression and anxiety

In Germany, the recognition rate of depression in the primary care sector has been reported at 74% [20]. Recognition rates among HF patients are likely to be lower because of the symptom overlap of non-specific HF symptoms and symptoms of depression. We are aware of one study investigating recognition rates of depression and anxiety in ambulatory HF patients. This study found that 42.5% of patients screened positive for depression and/or anxiety also had a diagnosis of depression or anxiety in their medical records [21]. However, that study almost exclusively included men (98.7%) and did not investigate the prognostic implication of recognition/treatment of depression/anxiety. Despite the purported clinical relevance of depression and anxiety, no intervention studies investigated the effects of depression and anxiety modification on the prognosis of HF patients in primary care settings. Further, the evidence base to support such trials is slim because so far there is no observational data underlining an association between recognition of depression and anxiety and the depression/anxiety-outcome [22], nor data underlining the cardiovascular outcome in primary care patients with HF [23-25].

As a result of these considerations, the aim of the study is to evaluate the state of psychosocial health care (recognized and unrecognized depression/anxiety and subsequent treatment) and its influence on health related quality of life and prognosis in primary care patients with HF.

Given that the prevalence rates of depression in HF patients vary due to differences in and the threshold levels of the assessment tools used, appropriate cut-off values for self-administered instruments measuring anxiety/ depression in HF patients will be derived in a sub-study.

## Methods/Design

The study is designed as a multicenter, prospective, observational study investigating 3,950 primary care patients with HF in Germany. The following research questions will be addressed:

● How many patients with HF suffer from depression and/or anxiety?

● How are the recognition rates of depression and/or anxiety by general practitioners (GPs)?

● How often are which measures taken by the GP when depression and/or anxiety are recognized?

● Is there an association between the presence of depression and/or anxiety and quality of life and HF prognosis (hospital admittance and mortality risk)?

● Is there an association between the recognition of present depression/anxiety by the GP and quality of life and HF prognosis (mortality, hospital admissions)?

● Which factors are associated with non-recognition and with failure to initiate adequate interventions (pharmacological or psychotherapeutical)?

● Is there an association between the presence and the recognition of depression/anxiety by the GP and health care aspects (e.g. frequency of contacts with the GP)?

### Recruitment

Recruitment takes place in two steps: First: primary care practices are recruited; and second: the participating GPs invite their patients to participate in the study. Two study centers, Hamburg and Würzburg, recruit general practices in four recruitment regions: Hamburg, Kiel, Lübeck (northern Germany) and Würzburg (southern Germany). The recruitment of the primary care practices began in April 2012 and will last until January 2014. All primary care practices in Hamburg, Kiel, Lübeck and Würzburg and within a 50 km radius of these cities, (to include urban and rural areas), receive a written invitation to participate in the study. If not responding to the invitation, study staff contacts each general practitioner by phone.

In a second step, participating GPs apply the following search criteria to identify eligible patients from the electronic records: age 18 and above, last consultation within the last six months, and any diagnosis of heart failure (ICD-Codes beginning with I50, I11.0, I13.0, I13.2) documented within the last 5 years. Out of all patients, who meet the mentioned criteria those who passed away since the last consultation or suffer from dementia are excluded (for a complete list of all inclusion and exclusion criteria see Table 1).

**Table 1 T1:** Inclusion and exclusion criteria

	**Observation group 1 (P+/+)**	**Observation group 2 P(+/−)**	**Observation group 3 P(−/−)**
**Inclusion Criteria**			
Informed consent	✓	✓	✓
Aged 18 years and older	✓	✓	✓
Diagnosis of heart failure within the last 5 years, validated by the GP on basis of his medical records	✓	✓	✓
At least one contact with the participating GP within the last 6 month	✓	✓	✓
Depression and/or anxiety	✓	✓	
Recognition of existing depression and/or anxiety by the GP	✓		
**Exclusion Criteria**			
Diagnosis of dementia given by the GP	✓	✓	✓
Not a regular patient of the participating GP’s practice	✓	✓	✓

All eligible patients are invited to participate in the study through a letter from their GP. This letter includes all written information regarding the study, as well as a consent form. Beside a study description, the patient information covers procedures of the study, data collection, processing and storage, as well as possibilities for withdrawal of consent. A phone number for contacting the study staff with questions and for further information is provided with the information package. The informed consent form is already provided with a randomly assigned ID number.

In case of interest, the patient sends the signed, informed consent form to the recruiting study center via a prepaid and pre-addressed envelope. The first patient was included in July 2012; the recruitment of patients will last until January 2014.

### Study endpoints

The primary outcome of this longitudinal study is the quality of life after 12-months of follow-up. The secondary outcome is the prognosis of heart failure in terms of hospital admissions and mortality risk within the 12-month follow-up period. Group comparisons will contrast patients with depression and/or anxiety recognized by the GP (observation group 1: P(+/+)), patients with depression and/or anxiety not recognized by the GP (observation group 2: P(+/−)) and patients without depression and/or anxiety whose GPs did not diagnose any depression or anxiety (observation group 3: P(−/−)). For further information see Table 1.

### Data collection

Data is collected at the baseline assessment and at the follow-up assessment 12 months later. In the baseline assessment the patient receives a self-administered questionnaire by mail (see Table 2), as well as a free return envelope. Five days after the questionnaire is sent the patients receive a reminder by mail. Based on the information provided in the questionnaire, the patients are assigned to one of three observation groups. For more details see section *Recognition of depression and anxiety*. The GP of each patient assigned to one of the observation groups is interviewed by study staff in a telephone-interview. During the interview the GP has access to all patient data in his or her medical records. The questions regarding depression and anxiety are collected along with a comprehensive list of further comorbidities (see Table 2).

**Table 2 T2:** Data collection

**BASELINE**	
**Patients: Self-administered questionnaires (by mail)**	
Depression	Patient Health Questionnaire 9-item Subscale Depression (PHQ-9) [26-28]/Hospital Anxiety and Depression Scale [29,30] – Subscale Depression (HADS-D)/PROMIS Depression Scale [31,32]
Anxiety	Patient Health Questionnaire 7-item Subscale Generalized Anxiety Disorder Assessment (GAD-7) [33-35]/Hospital Anxiety and Depression Scale [29,30] – subscale anxiety (HADS-A)/PROMIS Anxiety Scale [31,32]
Treatment of Anxiety and Depression	Medication intake/Utilization of psychotherapy or other therapies (e.g. music therapy, occupational therapy, relaxation training)
Social support	Lubben Social Network Scale (LSNS) [36]/ENRICHED Social Support Instrument (ESSI) [37]
Stress	Patient Health Questionnaire - Subscale Stress (PHQ-D) [26,38]
Compliance	Morisky Medication Adherence Scale (MMAS-8) [39-41]
Quality of life	EQ-5D-5 L [42]
Self-efficacy	General Self-efficacy Scale [43]
Lifestyle	Salt restriction: Do you pay attention to your diet?/Fluid intake: How much do you drink daily?/Weight control: How often do you weigh yourself?/Vaccination: Did you receive a flu shot within the last year? Have you been vaccinated against pneumonia?/Alcohol intake: At occasions you drink alcohol, how much alcohol do you consume on average?/Smoking status and cigarette consumption: If you smoke occasionally or regularly: How much do you consume on average?
Physical Activity/Capacity	How often do you engage in physical activity? Based on Verghese [44]/Self-rated physical capacity according to NYHA class
Socio-economic status	Household income per capita
Sociodemographic data	Gender/Age/Height/Weight/Type of insurance/Marital status/Status of living/ Nursing care/Employment status/ Education [45]/Migration status/ Citizenship
Contact to the GP	Last contact/Frequency of contacts within the last 6 month/Years of being patient of the actual GP
**GPs: Telephone-interview with insight in the medical record**	
Validation of heart-failure diagnosis	Does the patient have heart failure?/Severity level according to New York Heart Association (NYHA) class/Ejection fraction
Size of practice	Number of GPs in the practice/ Practice type (single practice/practice sharing/group practice)/Number of patients insured by the statutory health insurance per quarter/ Percentage of private patients
Familiarity with the patient	Are you the regular GP of the patient?/How well do you know the patient? (Scale 1 to 10)
Comorbidity	Charlson Comorbidity Index [46]/Which additional diseases does the patient have?
Depression/Anxiety	Does the patient have any symptomatology of depression/anxiety? If yes, please specify/Had the patient any symptomatology of depression/anxiety in the past?
Measures taken if depression/anxiety is recognized	What treatment have you prompted?
Treatment of heart failure	What difficulties have you encountered when treating the heart failure in this patient? Have there been any reasons to deviate from the recommended pharmacological treatment?
Sociodemographic data of the GP	Age/Gender/Years of practice/Speciality/Additional trainings
**12-MONTH FOLLOW-UP**	
**Patients: Self-administered questionnaire (by mail)**	
*All measures according to baseline; additional data:*	
Hospital admission within the last 12 month	Number of Hospital Admissions/Date of admission/Length of stay/Admission diagnosis/Emergency vs. pre-scheduled hospitalization
Change of GP	Did you change your GP within the last 12 month? If yes: How many months ago did you change your GP?

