**GP: Information from medical records (provided by phone)**	
Survival	Mortality within the last 12 month/Date of death/Course of death
Hospital Admission	Number of Hospital Admissions/Date of Admission/Length of stay/Admission diagnosis/Emergency vs. pre-scheduled hospitalization/

Since diagnosis of heart failure will be obtained from the electronic patient records, we will double-check that the heart failure diagnosis is correct at the beginning of the telephone interview with the GP. After validating the diagnosis, the GP is asked to specify the severity level of heart failure according to New York Heart Association (NYHA) functional class. For all further information collected see Table 2.

At the 12-month follow-up assessment the patient receives a second self-administered questionnaire by mail, while data in the general practice will be extracted from the medical records of the practice and are provided by either the GP or practice staff over the phone. For further details regarding the contents of the data collection please refer to Table 2.

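### Patient-reported admissions and GP-reported deaths are asked for over the 12 months before the follow-up contact, but the endpoint runs 12 months forward from baseline; tie every item to the baseline date

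*Protocol article*

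**What the plan says.** Under Study endpoints, the secondary outcome is "hospital admissions and mortality risk within the 12-month follow-up period". That period runs forward from baseline. Under Data collection, the timing is "Data is collected at the baseline assessment and at the follow-up assessment 12 months later", with no tolerance around the 12 months.

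The follow-up part of Table 2 lists three items for these events:

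- Patient questionnaire: "Hospital admission within the last 12 month", with number, dates, length of stay and diagnosis.
- GP, survival: "Mortality within the last 12 month/Date of death/Course of death".
- GP, admissions: "Number of Hospital Admissions/Date of Admission/Length of stay/Admission diagnosis/Emergency vs. pre-scheduled hospitalization". No period is printed in this row.

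For the GP items, "data in the general practice will be extracted from the medical records of the practice", and the answers are given by phone. The Abstract names the general practice as the provider of the hospitalization and mortality data. Data analysis plans one-year comparisons, Cox regression and Kaplan-Meier curves for these outcomes.

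**The concern.** A window that ends at the contact matches a window that starts at baseline only when the contact falls exactly 12 months after baseline. Follow-up is by post for patients and by phone for practices, so some spread around 12 months should be expected.

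With a late contact, the first weeks after baseline fall outside the patient item as worded, and weeks after month 12 are asked about instead. With an early contact, the item reaches back before baseline. The recorded dates allow surplus events to be removed. They cannot restore an admission that the patient was never asked about.

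At stake are the completeness of patient-reported admissions early in follow-up and the agreement between patient and practice reports, which may cover different periods for the same person. Time to first admission is the most exposed analysis: a missed early admission makes the patient look event-free, or moves the first event to a later date.

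**Working it through.** **The plan's own figures.** The article gives no event rate, event count or power for deaths or admissions, so there is no stated figure to reproduce for this endpoint. The recruitment chain in Sample size calculation does reproduce:

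- 10,973 × 0.40 × 0.90 = 3,950 baseline questionnaires
- 3,950 × 0.20 = 790 with depression and/or anxiety
- 790 × 0.85 = 671.5, against the stated 672

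None of these figures uses the recall window.

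**Windows side by side.** Let baseline be month 0 and the contact month 12 + d.

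| Source | Period covered |
|---|---|
| Endpoint | month 0 to 12 |
| Patient admissions, as worded | month d to 12 + d |
| GP mortality, as worded | month d to 12 + d |
| GP admissions | not printed |

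For d > 0, months 0 to d are not asked about. For d < 0, the item takes in |d| months before baseline and ends |d| months before month 12.

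**Share left out by a late contact, literal reading.** The delay d is an assumption throughout.

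With evenly spread events the share is d/12:

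- d = 0.5: 0.5/12 = 4.2%
- d = 1: 1/12 = 8.3%
- d = 2: 2/12 = 16.7%
- d = 3: 3/12 = 25%

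For first events with a constant hazard and 12-month risk F (also assumed), h = −ln(1 − F)/12 and the share is (1 − exp(−h·d))/F. For d = 1:

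- F = 0.10: h = 0.00878, so (1 − exp(−0.00878))/0.10 = 8.7%
- F = 0.40: h = 0.0426, so (1 − exp(−0.0426))/0.40 = 10.4%

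Over F = 0.10 to 0.40 the shares are 4.4–5.3% for d = 0.5, 8.7–10.4% for d = 1, 17.4–20.4% for d = 2 and 26–30% for d = 3. The loss is therefore about 8–10% of the year's events per month of delay, and zero when d = 0.

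These shares apply once events after month 12 are removed. If late events are kept, the item still spans 12 months and a constant admission rate gives about the same total count, but over a shifted period.

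**The case against.** The strongest reply is that Table 2 is a condensed content list in a journal article. Under a heading for the 12-month follow-up, a phrase about the last 12 months is natural shorthand for the follow-up period, and the forms themselves are not shown. This has weight: the loss follows only if the printed wording is the wording used, so the point is that events may be missed, not that they will be. It does not remove the mismatch between what is printed for the endpoint and what is printed for collection.

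The second reply is that the practice is the named source for these outcomes, and its admission row carries no limit. An early admission that the patient item leaves out may still come from the record with its date. This stands. It limits the loss to the patient report, though it also leaves the two sources without a common window.

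A reader might infer that deaths are lost in the same proportion. The documents do not support that. The row asks about survival, takes the date of death, and is answered from the record. For a death to be lost, a practice phoned at month 13 would have to leave out a death in month 1.

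A reader might also cite "Five days after the questionnaire is sent the patients receive a reminder by mail" as evidence of late follow-up. That sentence describes the baseline mailing, and five days would be only 5/365 = 1.4% of a year.

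**Conclusion.** The point holds as a mismatch of wording with a cheap remedy. Two Table 2 items look back from the contact, the endpoint looks forward from baseline, and the GP admission row gives no period. Under the literal reading, patient-reported admissions may lose about 8% of the year's events per month of delay if events are evenly spread, or about 9–10% with a constant hazard and an assumed annual risk of 10–40%. Neither the delay nor the risk is in the article, so the actual loss cannot be derived and may be close to zero.

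A reader might go further and infer a biased comparison of recognized with unrecognized patients. For example, if contacts were one month late in P+/+ and two months late in P+/−, equal true rates would give an observed ratio of (12 − 1)/(12 − 2) = 1.10 after trimming. Nothing in the article supports such a difference. Both groups have depression and/or anxiety, so slower return of questionnaires by such patients would not separate them, and practice calls do not depend on when a questionnaire is returned.

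Only the secondary outcome is touched. The primary EQ-VAS outcome and the sample size stand as they are.

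**What to change.** Word every patient and GP follow-up item on deaths and admissions as *since (date of baseline assessment)*. Pre-print the patient's own date on the questionnaire and have the interviewer read it out to the practice. Give the GP admission row the same window as the patient item. In the analysis, count events from that date to 12 months, using the admission and death dates already collected, and leave out anything before or after.

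Because the baseline questionnaire and the GP interview fall on different days, state once which date counts as baseline for this purpose. Starting the event clock at the GP interview, when the group is fixed, is a separate and debatable choice that this change does not require.

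The cost is a merged date on the forms and a slightly longer recall period for patients contacted late.
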